Therefore, the aim of the present pilot intervention study will be to evaluate the feasibility and proof-of-concept of a CBT-AR based digital intervention “ExpeditionFood” for children and their parents/caregiver(s). Since sensory sensitivity is the most prevalent presentation of ARFID (4–6), the digital intervention will focus on individuals with sensory sensitivity. Based on the reported high prevalence in children ages 8–14 years (3, 4), the study will include children in this age range. Consequently, this study will simultaneously evaluate the feasibility of CBT-AR for a slightly younger age than in previous CBT AR trials (aged >10 years). Additionally, none of the previous cited interventions have been evaluated in German speaking countries where ARFID prevalence has been established (4, 20, 21). Hence, the primary aim of this study is to assess feasibility in German speaking countries and identify effect sizes for future randomized control trial. We hypothesize that a digital family supported intervention for children with ARFID will be feasible with acceptable recruitment and dropout rates and accepted by children and caregivers. Additionally, we hypothesize that the digital intervention will reduce ARFID symptoms, food neophobia and psychosocial impairment from pre- to post-intervention and will also increase quality of life. Finally, we will investigate if these effects are maintained until the four-week follow-up.

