### Design

2.1

We will conduct a single-arm clinical trial to evaluate the feasibility of a digital therapist-guided CBT-AR intervention for children with ARFID and their parents/guardians. The 12-week intervention will be based on the original manualized CBT-AR intervention translated to German. The CBT-AR specific food exposure strategies for sensory sensitivity will be delivered via a mixture of video therapy sessions and self-guided modules (14). Based on the reported high prevalence in children ages 8–14 years (3, 4), the study will focus on this age range. As CBT-AR has been developed from the age of 10 years on, we made a few adaptions to adopt for the slightly younger age range. Firstly, to decrease treatment burden on the children with often lower treatment motivation (23), we will offer self-guided sessions for parents/guardians and the child will join for the family supported video therapy sessions only. Secondly, we developed psychoeducational materials for the different ages with psychoeducational stories to enhance engagement of the younger children and different aged case examples. We will assess primary and secondary outcomes at pre-assessment/baseline, mid-assessment, post-assessment and 4-week follow up. Parents/guardians and children will be gifted a small coupon for completing the assessments. No incentive will be provided for participation in the intervention itself. Furthermore, the study is registered in the German Registry of Clinical Studies (Deutsches Register Klinischer Studien: DRKS00038026).

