#### Clinical outcomes

2.9.1

As proof of concept, we will assess ARFID symptoms. We will therefore administer the Nine Item Avoidant/Restrictive Food Intake disorder screen (NIAS (35, 43)) and a shortened version of the Food Neophobia Scale (FNS (44, 45)) at each time point. Additionally, we will use the parent- and child- version of the ARFID module of the ChEDE (33) to assess the fulfilment of ARFID criteria and to assess ARFID presentation. The subscales psychosocial impairments and sensory sensitivity will be used as an indicator for reduction in ARFID symptoms according to expert-ratings. Additionally, we will examine exploratory the subscales ChEDE lack of interest and fear of negative consequences to examine if changes in sensory sensitivity also affect the other presentation (19). Furthermore, the number of integrated foods will be reported as a treatment outcome based on parents’ report.

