#### Additional measures

2.9.2

Parents and Children will complete demographic characteristics assessment (e.g., gender, age, ethnicity) and psychiatric/medical history. Furthermore, we will assess comorbid diagnosis by both diagnostic interviews and the self-report measures assessing depression (Children’s Depression Screeners (46)) and anxiety levels (State–Trait Anxiety Inventory (STAI) (47)). Furthermore, we will record video therapy sessions to check for adherence of the study therapist to the intervention. See **Table 2** for a detailed overview including other variables of interest that are not part of the main analysis.

**Table 2 T2:** Overview over measures and measuring points.

Instrument	Author (German-language version)	Construct	Number total items	Subscales	Scale	Caregiver					Children				
						Measuring points					Measuring points				
						0	1	2	3	4	0	1	2	3	4
Primary outcomes (Feasibility)															
Credibility/expectancy Questionnaire	(42)	Treatment expectancy and credibility	6	Expectancy; Credibility	9-point Likert scale from 1 = not at all to 9 = very; 11-point Likert scale from 0 to 100%		x	x	x						
Credibility/Expectancy	Adopted from (48)	Treatment expectancy	1	How sure are you that participating in ExpeditionFood will help you with your eating problems?	9-point Likert scale from 1 = not at all to 9 = very;							x	x	x	
Client satisfaction questionnaire, adapted for inpatient fields of work	(49)	Satisfaction with treatment service	8	/	4-point Likert scale; different scales (e.g., 1 = “excellent” to 4 “bad”			x	x				x	x	
Adverse Events	Adopted from (41)	Adverse events related to the intervention	3		1 Yes/no item; 1 open item to describe the event; 2 severity items on a 4-Point Likert scale 1= not at all to 4= very much		x	x	x	x		x	x	x	x
Secondary outcomes (Measures of ARFID)															
Eating Disorder Examination (EDE) ARFID module	(33)	DSM-5 based diagnosis of ARFID		Includes items on sensory sensitivity and psychosocial impairment	Expert-Rating: Criterion Present Yes/No, symptom severity 0-6		x		x			x		x	
Nine Item Avoidant/Restrictive Food Intake disorder screen (NIAS)	(35, 43) Translated with permission.	Symptom of ARFID	9	picky eating, appetite, fear	6-Point Likert scale 0 = Strongly Disagree to 5 = Strongly Agree.	x	x	x	x	x		x	x	x	x
Food Neophobia Scale (FNS) (shortened version)	(44, 45)	Food Neophobia	7		7-point Likert scale ranging from 1= “strongly disagree” to 7 =“strongly agree.”	x	x	x	x	x		x	x	x	x

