Diagnostic Interview for Mental Disorders in Children and Adolescents	(36)	Diagnosis of comorbid symptoms (DSM-5)			Criterion fulfilled yes/partially/no		x								
Children’s Depression Screeners (ChilD-S)	(46)	Depression	8		4 Point Likert scale; 0 = “agree” to 3 = “disagree”							x	x	x	x
State–Trait Anxiety Inventory—Child version trait subscale	(47)	Trait Anxiety	20		3-response scale							x	x	x	x
Generic Quality of Life Instrument for Children-Revised-	(51)	Health-related quality of life	24	Physical well-being psychological wellbeing, self-esteem, family, friends, education/school	5-point Likert scale from 0 = “never” to 4 = “always”							x	x	x	x
Working alliance inventory—short revised	(52, 53)	Therapeutic alliance	12		5-point Likert scale from 1 = “rarely” to 5 “always”			x	x	x					
Therapeutic Alliance Scales for Children	(54)	Therapeutic alliance	12	Bond/working alliance; Positive and negative aspects of the emotional bond	4-Point Likert scale from 1 = “not at all” to 4 = exactly right”								x	x	x
Additional measures															
Children Eating Disorder Examination-Questionnaire (EDE-Q8)	(55, 56)	eating disorder psychopathology	8	restraint, eating concern, weight concern, and shape concern	0–6 scale = number of days in the previous 28; or (b) “Not at all” to “Markedly, ratio scale	x						x	x	x	x
Children Eating Disorder Examination-Questionnaire Parent version (EDE-QP-parent version)	(56)	eating disorder psychopathology	28	restraint, eating concern, weight concern, and shape concern	0–6 scale = number of days in the previous 28; or (b) “Not at all” to “Markedly, ratio scale	x									
The Affinity for Technology Interaction (ATI) Scale	(57)	Affinity for Technology Interaction	9		6-point Likert scale, 1 = “strongly disagree” to 6 = “strongly agree”		x								

ARFID, avoidant/restrictive food intake disorder. Assessment will take place at screening (t0), baseline (t1), mid-intervention (t2), post-intervention (t3) and 4-week follow-up (t4). Additionally, parents will be asked to fill out weekly the FNS; NIAS, and adverse event scale. Furthermore, number of integrated new foods will be tracked by caregivers from week 3 onwards. Demographic characteristics (e.g., gender, age) will be assessed at screening and baseline and parent-child interaction regarding food at pre-, mid and post-treatment.

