### Proposed statistical analysis

2.10

As our primary aim is to assess feasibility, we will report recruitment rates and retention rates and number of adverse events until post-assessment with descriptive statistics. We will also report feasibility ratings of parents regarding the duration of sessions and materials, number of foods tasted per week, as well as the overall therapy duration of individuals completing the intervention. Acceptability will be descriptively reported based on parents rating on the treatment credibility (Credibility/Expectancy Questionnaire (CEQ) (48) and treatment satisfaction (Client Satisfaction Questionnaire (CSQ) (49)), as well as single-items for children.

As a secondary aim we will analyze ARFID symptoms reduction with paired sample t-test for expert-rated psychosocial impairment and sensory sensitivity (based on the Eating Disorder Examination (EDE) ARFID module, as well as self-report measures of symptoms of ARFID (i.e., Nine Item Avoidant/Restrictive Food Intake disorder screen (NIAS) (43) and Food Neophobic Scale (FNS) (44)) and children’s quality of life will be conducted from pre- to post assessments and pre-to follow-up.

Exploratory, in line with previous research we will also analyze anxiety (STAI (47)) and depression levels (Children’s Depression Screeners (46)) using dependent t-tests to test for potential changes in comorbid symptoms (12, 15).

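### Expert-rated ARFID subscales appear in the pre-to-follow-up tests of section 2.10, but Table 2 schedules the interview only at baseline and post-treatment

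*Protocol article*

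**What the plan says.** Section 2.10 plans a "paired sample t-test for expert-rated psychosocial impairment and sensory sensitivity", taken from the ARFID module of the Eating Disorder Examination. It continues in the same sentence with NIAS, FNS and children's quality of life, and closes with "quality of life will be conducted from pre- to post assessments and pre-to follow-up".

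Section 2.9.1 gives the role of the interview: "The subscales psychosocial impairments and sensory sensitivity will be used as an indicator for reduction in ARFID symptoms according to expert-ratings". Table 2 describes the module as "Expert-Rating: Criterion Present Yes/No, symptom severity 0-6" and marks its measuring points. The table note defines t1 as baseline, t3 as post-intervention and t4 as the 4-week follow-up.

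Section 2.1 states in general terms: "We will assess primary and secondary outcomes at pre-assessment/baseline, mid-assessment, post-assessment and 4-week follow up".

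The Introduction hypothesises that ARFID symptoms, food neophobia and psychosocial impairment fall between pre- and post-intervention and that quality of life rises. It then adds: "Finally, we will investigate if these effects are maintained until the four-week follow-up".

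**The concern.** An analysis is planned at a time point for which the assessment table shows no measurement. If Table 2 is followed, the expert-rated part of the follow-up analysis cannot be run. The gap would be noticed only at analysis, when an interview not held at t4 can no longer be recovered.

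Psychosocial impairment is affected most, because the ChEDE subscale is the only listed instrument for it. Sensory sensitivity is affected less. The NIAS picky-eating subscale is available at t4 as a partial questionnaire substitute, but the article itself says that the NIAS is not yet validated in German.

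A second, smaller issue concerns the scales that do have a t4 value. The aim is worded as maintenance, but the only follow-up contrast stated is pre versus follow-up. That contrast shows whether scores still differ from baseline. It does not show how much changed after treatment ended.

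**Working it through.** **Step 1: planned contrasts against scheduled data.** Each Table 2 row was split into its ten measuring-point cells (caregiver t0 to t4, child t0 to t4) and compared with what section 2.10 needs.

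| Outcome in section 2.10 | Caregiver | Child | t1 to t3 possible | t1 to t4 possible |
|---|---|---|---|---|
| ChEDE psychosocial impairment, sensory sensitivity | t1, t3 | t1, t3 | yes | no |
| NIAS | t0 to t4 | t1 to t4 | yes | yes |
| FNS | t0 to t4 | t1 to t4 | yes | yes |
| Quality of life | none | t1 to t4 | yes | yes |

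The NIAS and FNS rows, next to the ChEDE row, carry t4 marks for both informants. Text extraction damage is therefore an unlikely explanation for the missing ChEDE mark.

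**Step 2: consequence.** A paired t-test uses the within-child difference d = (value at t4) − (value at t1). Under Table 2 no ChEDE value exists at t4, so d is undefined for every child. The number of pairs is 0 out of a planned 40 for each of the two expert-rated subscales.

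**Step 3: can another passage settle it?** Section 2.1 implies that all secondary outcomes are measured at mid-assessment and follow-up, whereas the ChEDE row has neither. Section 2.1 cannot be taken as an instrument-level schedule, because some primary outcomes also fail to match it. In Table 2 the credibility/expectancy items have no t4 mark, and the satisfaction questionnaire has neither t1 nor t4. Section 2.9.1 says NIAS and FNS are given at each time point and introduces the ChEDE separately, without time points. No passage therefore decides whether a t4 interview takes place.

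**Step 4: what a pre-to-follow-up test shows about maintenance.** The article gives no figure for this, so the following is an illustration under assumed effects. Assume a standardised paired effect dz of 0.8 at post-treatment and 0.4 at follow-up, i.e. half of the gain lost. Section 2.3 gives N = 40 and expects 20–30% dropout, so the number of pairs runs from 40 × 0.70 = 28, through 40 × 0.80 = 32, to 40 with no dropout. For a two-sided test at 0.05, the probability of significance comes from the noncentral t distribution with n − 1 degrees of freedom and noncentrality 0.4 × √n:

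- n = 28: noncentrality 2.12, critical t 2.05, probability 0.53
- n = 32: noncentrality 2.26, critical t 2.04, probability 0.59
- n = 40: noncentrality 2.53, critical t 2.02, probability 0.69

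Under these assumptions, the pre-to-follow-up test would still be significant in about 53% to 69% of trials although half of the benefit had gone.

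**The case against.** The sentence in section 2.10 is grammatically broken, and the follow-up contrast could be attached to quality of life alone. That ambiguity is real. The list-wide reading is still the more natural one, and on the narrow reading the Introduction's maintenance aim continues to cover psychosocial impairment.

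A reader might infer that the hypothesis on psychosocial impairment is untestable. The documents do not support that. The hypothesis is worded pre to post, and the ChEDE is scheduled at exactly those two points. What is at risk is the separate follow-up question.

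A reader might also conclude outright that maintenance of psychosocial impairment cannot be answered. That holds only if Table 2 governs. Sections 2.1 and 2.10 point the other way, so what the documents show is an unreconciled conflict. Equally, section 2.1 is better read as a general list of visits than as a firm contradiction of Table 2.

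On the maintenance contrast, the article never says that a significant pre-to-follow-up test will be taken as proof of maintenance. Whether an effect is still present relative to baseline is a legitimate question, and the two planned contrasts can be compared descriptively. The percentages in the illustration rest on effect sizes found nowhere in the article and say nothing about the ChEDE gap. These points stand, and they make the t3-to-t4 contrast the lesser part of this comment.

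Finally, these are secondary outcomes in a feasibility trial whose authors already warn that power may not suffice for conclusions on efficacy. That lowers the severity but does not remove the mismatch. An analysis plan cannot supply data that were not collected.

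**Conclusion.** The mismatch is real and of moderate weight. On the natural reading of section 2.10 and under the Table 2 schedule, two planned pre-to-follow-up tests have no data. These are expert-rated psychosocial impairment and expert-rated sensory sensitivity. The loss is the maintenance question for psychosocial impairment and the expert rating of sensory sensitivity at t4.

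The primary feasibility outcomes, the sample size and all pre-to-post tests are untouched. Follow-up remains covered by NIAS, FNS and quality of life. For those scales, the planned contrast does not isolate change after treatment ends. The 53% to 69% range shows how far that could matter, but only under the assumed dz of 0.8 and 0.4.

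**What to change.** Reconcile sections 2.1 and 2.10 with Table 2 before families reach follow-up.

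1. In section 2.10, restrict the pre-to-follow-up tests to NIAS, FNS and quality of life. State that the ChEDE subscales are analysed from t1 to t3 only and that their maintenance, including that of psychosocial impairment, is not assessed.
2. In section 2.1, say that the measuring points differ by instrument and refer to Table 2.
3. For NIAS, FNS and quality of life, add the t3-to-t4 mean change with its 95% CI as the description of maintenance.

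All three are wording changes and use data already scheduled. If the sponsor wants expert-rated maintenance answered, the alternative to item 1 is to schedule the ChEDE at t4 and mark it in Table 2. That is optional and costs one more interview per family.

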### Recruitment and sample size

2.3

Recruitment will take place in Germany, Switzerland, Austria where German is (at least one of) the officially spoken languages. We will recruit families via the study’s website, social media (e.g., Instagram, Facebook), flyers, articles in our university press, and advertisements provided to outpatient health care providers affiliated with Konstanz University.

We conducted a power analysis with G*Power (version 3.1) to estimate a sample size, and also considered the sample sizes used in previous one-arm CBT-AR trials (10, 11, 15, 34). Hence, we based our power analysis on a = 0.05 and 1-b = 0.95, and a medium-sized effect size of f = 0.6, which resulted in a sample size of n = 32. To account for an expected dropout rate of 20-30% (15), we will aim to recruit *N* = 40. However, as the primary aim is to assess overall feasibility and acceptability and our main secondary aim is to identify effect sizes for randomized control trials, we are aware that depending on dropout rates the power might not be sufficient to make conclusions about the efficacy.

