### Assessment and data management

2.7

We will assess at screening (t0), baseline (t1), mid-intervention after completion of session 6(t2), post-intervention after completion of session 12(t3) and 4-week follow-up (t4). We will use German translations of all questionnaires. Additionally, parents/guardians will complete brief weekly measures after every session. Self-report data will be assessed via Qualtrics (i.e., for outcome measures, Qualtrics, 2025) and participants will be asked to provide only their assigned participant code when answering the questions. Only the internal study team will have access to the key file in digital password protected folder to link the participants code to the names. Additionally, the secure health platform Curafida (ZTM Bad Kissingen GmbH, 2025) will integrate the software MyMedax for content and reflection questions in self-guided sessions. We will use the secure video call software webPRAX for video call sessions (Healthy Projects GmbH, n.d.). We created a data protection policy and a register of all processing activities with the legal office of Konstanz University for this study. Moreover, a data protection and confidentiality agreement will be in place between the company of the health platform ZTM Bad Kissingen GmbH and the University of Konstanz.

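### The planned pre-to-follow-up test shows that children are still better than at baseline; it does not show that the post-treatment gain was kept, which is the stated follow-up question

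*Protocol article*

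**What the plan says.** The Introduction first hypothesises improvement from before to after the intervention in ARFID symptoms, food neophobia, psychosocial impairment and quality of life. It then adds: "Finally, we will investigate if these effects are maintained until the four-week follow-up". The effects in question are therefore the pre-to-post changes.

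The section Proposed statistical analysis states that "we will analyze ARFID symptoms reduction with paired sample t-test for expert-rated psychosocial impairment and sensory sensitivity". It extends the same test to the NIAS, the FNS and children's quality of life, and says that the tests "will be conducted from pre- to post assessments and pre-to follow-up". Those are the only two contrasts named. The article gives no post-to-follow-up comparison, no model across time points, no definition of maintenance and no largest acceptable loss.

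Table 2 schedules the NIAS, the FNS and quality of life at both t3 and t4. It schedules the ARFID module of the Eating Disorder Examination at t1 and t3 only.

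**The concern.** Whether a gain is kept depends on what happens between the end of treatment and follow-up. The planned follow-up test compares follow-up with baseline. Rejecting its null shows that some benefit remains, not how much of the post-treatment benefit remains. The article goes beyond leaving detail open: it names the contrast for this aim, and that contrast answers a different question.

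At stake is how the follow-up result is reported. A significant pre-to-follow-up test could be taken as evidence of maintenance when part of the benefit has been lost within four weeks. The error can also run the other way: a non-significant test could be taken as relapse when the gain was fully kept and the sample was simply small.

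**Working it through.** **Inputs from the article (Recruitment and sample size).** "we based our power analysis on a = 0.05 and 1-b = 0.95"; "a medium-sized effect size of f = 0.6, which resulted in a sample size of n = 32"; the recruitment target is N = 40 with an expected dropout of 20-30%, which leaves 40 × 0.8 = 32 down to 40 × 0.7 = 28 families. Whether tests are one- or two-sided is not stated.

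**Assumptions.** The 0.6 is read as a paired standardised change (mean change divided by the SD of the change). The SD of the pre-to-follow-up change is not given and is taken as equal to the SD of the pre-to-post change.

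**Reproducing the plan's figure.** Exact paired t-test power uses the noncentral t distribution with df = n − 1 and noncentrality 0.6 × √n. One-sided at 0.05, the smallest n with power of at least 0.95 is 32 (power 0.953), which matches the article. Two-sided, n would be 39, and the power at 32 is 0.908. Reading 0.6 as Cohen's f in a one-group repeated-measures F test gives n between 8 and 21 (2 to 4 time points, correlation 0 or 0.5), which does not match. The paired reading is therefore used, and results are given for both one- and two-sided tests.

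**Step 1: observed loss that still leaves p<0.05.** The smallest significant observed standardised change is t_crit/√n.
- n = 32, one-sided: 1.70/5.66 = 0.30. Loss tolerated: 1 − 0.30/0.60 = 50%.
- n = 32, two-sided: 2.04/5.66 = 0.36. Loss tolerated: 1 − 0.36/0.60 = 40%.
- n = 28: the thresholds are 0.322 and 0.388, so the tolerated losses are 46% and 35%.

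These are observed changes. A true loss of that size does not guarantee significance, which is why Step 2 is needed.

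**Step 2: probability that the pre-to-follow-up test is significant, by true loss.** Noncentrality is 0.6 × (1 − loss) × √n.

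| True share of the 0.6 gain lost | n = 32, one-/two-sided | n = 28, one-/two-sided |
|---|---|---|
| none | 0.95 / 0.91 | 0.93 / 0.86 |
| 25% | 0.80 / 0.69 | 0.75 / 0.63 |
| 50% | 0.51 / 0.38 | 0.46 / 0.33 |
| 75% | 0.21 / 0.13 | 0.19 / 0.12 |

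If the true post-treatment effect were 1.0 (an assumption, not a figure in the article) and half were lost, leaving 0.5, the probability at n = 32 would be 0.87 one-sided or 0.78 two-sided.

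The first row shows the opposite error. At n = 28 with the whole gain retained, the test misses significance with probability 1 − 0.93 = 0.07 one-sided or 1 − 0.86 = 0.14 two-sided.

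**Step 3: what the direct contrast would deliver.** The SD of the t3-to-t4 change is not given; it is assumed to be 0.5 to 1.0 times the SD of the pre-to-post change. The half-width of the 95% interval, as a share of the planned gain, is t_crit × k/√n ÷ 0.6, with k the SD ratio.
- n = 32: 2.04 × 0.5/5.66 ÷ 0.6 = 30%, up to 60% at k = 1.0.
- n = 28: 32% to 65%.

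Two-sided power of a t3-to-t4 test to detect a loss of half the gain at n = 32 is 0.91 at k = 0.5 and 0.38 at k = 1.0. A non-significant result would therefore not establish maintenance.

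**The case against.** Maintained is not defined, and it could loosely mean still better than baseline, which the planned test does address. That reading is possible, but the article does not adopt it, and its sentence refers back to the pre-to-post effects.

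The plan is also not blind to relapse. Identifying effect sizes is its main secondary aim, and if standardised changes are reported for both contrasts, a fall from 0.6 to 0.3 would be visible. This stands in part: the two numbers would hint at a loss, but without an interval for the change between them.

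Three stronger readings are tempting and are not supported:
- **That the follow-up test will stay significant even after most of the gain has gone.** At the planned effect and 32 pairs, a true loss of half leaves significance at about even odds one-sided and less two-sided; a loss of 75% leaves 0.21 or 0.13. Higher probabilities need a smaller loss or a larger initial effect than planned.
- **That the trial will declare maintenance from a significant pre-to-follow-up p-value.** The article says only that maintenance will be investigated and states no such rule.
- **That the two tests will use different families and so mix relapse with dropout.** This could happen if families leave between t3 and t4, but the article states no analysis set, a matter commonly left to a fuller document.

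Finally, the article already warns that power may not suffice for conclusions about efficacy. That caution concerns precision. It does not cure a contrast aimed at another question, since with more families a smaller residual benefit would reach significance.

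**Conclusion.** The concern holds in a limited form. The stated follow-up question and the planned follow-up contrast do not match: the test can be significant with part of the gain lost, and it can miss significance with the gain intact, so its p-value is a poor guide to maintenance. The sizes in the working depend on reading 0.6 as a paired effect, on equal SDs of the change scores and on 28 to 32 pairs; the mismatch itself depends on none of these.

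Severity is minor. The recruitment, retention, adverse-event and acceptability outcomes are unaffected, the question is secondary in a feasibility trial, and no data collection needs to change.

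**What to change.** In section 2.10, for the NIAS, the FNS and quality of life, add the within-family change from t3 to t4 with its 95% confidence interval, in families with both assessments. Report it beside the t1-to-t3 change in the same families, so that the loss can be read against the gain without a change of sample. State that any conclusion on maintenance rests on this estimate and interval, and neither on the pre-to-follow-up p-value nor on a non-significant t3-to-t4 test. Keep the pre-to-follow-up comparison as a supporting result.

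The expert-rated psychosocial impairment and sensory sensitivity scores cannot be covered, because Table 2 schedules that interview at t1 and t3 only; the text should limit the maintenance question to the measures collected at t4.

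The cost is a few sentences and one further contrast on data already planned, with no added burden for families. The downside is that with 28 to 32 families the interval may be wide, so the maintenance statement may be inconclusive or less favourable.
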